## Economic evaluation

Within-trial health economic evaluation will be undertaken to assess cost-effectiveness of NAT-C vs usual care. The cost–utility analysis will be conducted alongside the trial and follow National Institute for Health and Clinical Excellence reference case for health technology appraisals.^26^ The main health outcome will be quality-adjusted life-years (QALYs) based on the Euroqol- 5 Dimension (EQ-5D-5L) (base case). Supplementary analyses will estimate cost per improvement in ICEpop CAPability Supportive Care Measure (ICECAP-SCM) and Carer Experience Scale (CES).

We will fully cost intervention delivery and measure service utilisation using a bespoke RUQ and measure outcomes using the EQ-5D-5L, ICECAP-SCM and CES at 1, 3 and 6 months.

A patient-completed RUQ will gather data on community-based (eg, contact with GPs, nurses and physiotherapists/occupational therapists), specialist palliative care (hospice, hospital or community) and hospital-based (eg, A&E visits and hospital attendances) healthcare resource utilisation at follow-up. Participants will be given a diary planner to keep to note any healthcare attendances to facilitate completion of the RUQ. Costs will be estimated using UK NHS reference unit costs, data from the Personal Social Services Research Unit and British National Formulary. The primary perspective is the health and personal social service provider but a secondary analysis will adopt a wider perspective to incorporate costs and productivity loss incurred by patients and carers.

Results will be presented as incremental cost-effectiveness ratio (ICERs). Results will also be presented as expected net monetary benefit and cost-effectiveness acceptability curves based on non-parametric bootstrapping.^27^ The analysis will employ regression models to adjust for baseline imbalances and account for the correlation between costs and QALYs.^28^ The analysis will assume a willingness to pay threshold of £20 000 per incremental QALY with ICERs below this value indicating cost effectiveness.

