**Methods and analysis:**

Cluster randomised controlled trial with internal pilot and embedded process evaluation to test the clinical and cost effectiveness of the NAT-C in primary care for people with active cancer in reducing unmet patient and carer need, compared with usual care. We will recruit 1080 patients with active cancer (and carers if relevant) from 54 general practices in England.

Participating practices will be randomised 1:1 to either deliver an NAT-guided clinical consultation plus usual care or to usual care alone. Consenting participants with active cancer and their carers (if nominated) will be asked to complete study questionnaires at baseline, 1 and 3 months for all, 6 months except for those recruited outside of the last 3 months of recruitment, and attend an NAT-C appointment if allocated to an intervention practice. An internal pilot will assess: site and participant recruitment, intervention uptake and follow-up rates. The primary outcome, the proportion of patients with an unmet need on the Supportive Care Needs Survey Short Form 34 at 3 months postregistration, will be analysed using a multilevel logistic regression. Mixed-methods process evaluation informed by Normalisation Process Theory will use quantitative survey and interview data from clinicians and key stakeholders in cancer care to develop an implementation strategy for nationwide rollout of the NAT-C if the intervention is cost-effective.

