## Statistical considerations

### Sample size

The study has been powered to detect improvement in patients’ level of unmet need as measured by proportion of patients reporting at least one moderate or high need in domains of the Supportive Care Needs Survey Short Form 34 (SCNS-SF34).^22^

Assuming that the proportion of patients with an unmet need on any SCNS-SF34 domain will be similar to that observed pre-intervention by Waller 2012^3^: 64%, then a sample size of 1080 patients recruited from approximately 54 general practices (540 patients, 27 practices per arm), will provide 85% power with a 5% significance level to detect a relative difference of 22% in the proportion of patients with an unmet need. This is an absolute difference of 14%, from 64% to 50%.

The sample size assumes: a 20% loss to follow-up rate by 3 months, to account for eligible patients who are, or are nearing, end of life; an intracluster correlation coefficient (ICC) of 0.05; an average general practice size of 20; and an adjustment to account for variable practice sizes of 4–40. Given heterogeneity in the design of palliative care services and availability of resources through general practices, and median ICCs reported for outcome variables (0.03) and primary care settings (0.045), an ICC of 0.05 will be used.^23^

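### The ICER rule is not limited to a positive QALY difference, so read literally it reverses the verdict when the estimated difference is negative

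*Protocol article*

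**What the plan says.** The Economic evaluation section plans a within-trial cost–utility analysis that will "follow National Institute for Health and Clinical Excellence reference case for health technology appraisals". QALYs come from the EQ-5D-5L, and the plan is to "measure outcomes using the EQ-5D-5L, ICECAP-SCM and CES at 1, 3 and 6 months". Under Participant questionnaires, the 6-month assessment does not apply to those registered in the last 3 months of recruitment.

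The results are to be given as ICERs. The section then adds: "Results will also be presented as expected net monetary benefit and cost-effectiveness acceptability curves based on non-parametric bootstrapping". It closes with a "willingness to pay threshold of £20 000 per incremental QALY", "with ICERs below this value indicating cost effectiveness". That closing clause is the only place in the section where a result is linked to a verdict. It sets no condition on the sign of the QALY difference, and the section does not mention dominance or the quadrants of the cost-effectiveness plane.

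The Abstract (Methods and analysis) says that the process evaluation will "develop an implementation strategy for nationwide rollout of the NAT-C if the intervention is cost-effective".

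**The concern.** An ICER is a ratio, and dividing by a negative number turns an inequality round. A ceiling on the ICER is a valid test only when the new option gains QALYs. If NAT-C cost more and lost QALYs, its ICER would be negative, hence below £20 000, and the stated rule would call it cost-effective although usual care dominates. If NAT-C saved a little and lost QALYs, a positive ICER below £20 000 would mean that the saving is too small to compensate, yet the rule would again call it cost-effective.

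The section would then hold two opposite answers for one result, one from the ICER sentence and one from net monetary benefit, with nothing prespecified to say which decides. A prespecified criterion is there to prevent this, and the Abstract makes the implementation strategy depend on the answer.

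**Working it through.** **1. Inputs.** From the Economic evaluation section: λ = £20 000 per QALY, and the rule ICER < λ. From Sample size: "1080 patients recruited from approximately 54 general practices (540 patients, 27 practices per arm", 20% loss by 3 months, ICC 0.05, mean practice size 20, range 4–40. Not in the document, and therefore assumed below: the utility SD, the true utility effect and the design effect for QALYs.

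**2. The plan's own figure.** The economic section states no computed figure. The sample size is rebuilt only because step 5 borrows its inputs.
- 64% versus 50%, two-sided 5%, 85% power: 223 per arm before clustering.
- Analysed cluster size 20 × 0.8 = 16. CV 0.45, assumed as a quarter of the range over the mean: (36/4)/20.
- Design effect = 1 + ((1 + 0.45²) × 16 − 1) × 0.05 = 1.912.
- Total = 2 × 223 × 1.912 / 0.8 ≈ 1066, close to the stated 1080.
- Analysed per arm: 540 × 0.8 = 432.

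**3. Algebra.** Let ΔC and ΔQ be the incremental cost and QALYs, and NMB = λΔQ − ΔC.
- If ΔQ > 0: ΔC/ΔQ < λ ⇔ ΔC < λΔQ ⇔ NMB > 0. The rule and NMB agree.
- If ΔQ < 0: ΔC/ΔQ < λ ⇔ ΔC > λΔQ ⇔ NMB < 0. The rule and NMB disagree in every case, ties aside.

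In 1 000 000 simulated pairs, agreement was 100% for ΔQ > 0 and 0% for ΔQ < 0.

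**4. Examples with a QALY loss.**

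| ΔC | ΔQ | ICER | Stated rule | NMB at £20 000 | NMB verdict |
|---|---|---|---|---|---|
| +£100 | -0.005 | -£20 000 | cost-effective | -100 − 100 = -£200 | not cost-effective |
| -£50 | -0.005 | £10 000 | cost-effective | -100 + 50 = -£50 | not cost-effective |
| -£60 | -0.002 | £30 000 | not cost-effective | -40 + 60 = +£20 | cost-effective |

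The third row shows that the error can also run against NAT-C.

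**5. How often might the estimate be negative?** Assume a utility difference δ that is constant over the horizon. ΔQ and its standard error then scale by the same factor, so the result is the same at 3 and at 6 months:

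P(ΔQ < 0) = Φ(−δ/SE), with SE = SD × √(2 × DE/432).

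- Lower end: SD 0.15, DE 1 gives SE = 0.0102. At δ = 0.01, Φ(−0.98) = 16%.
- Upper end: SD 0.30, DE 1.91 gives SE = 0.0282. At δ = 0.01, Φ(−0.35) = 36%.

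| True utility difference | Chance of a negative estimate |
|---|---|
| 0 | 50% |
| 0.01 | 16–36% |
| 0.02 | 2.5–24% |
| 0.03 | 0.2–14% |
| 0.05 | 0–4% |

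**The case against.** The strongest reply is that the safeguard stands in the same paragraph. Expected net monetary benefit and acceptability curves are planned, they are right in every quadrant, and a health economist working to the reference case would be expected to recognise a dominated result. A price per incremental QALY also suggests a QALY gain, where the rule is correct, and a journal article may leave the handling of quadrants to a fuller document. All of this bears on the likely damage, and it keeps the point minor. It does not remove the point: the article states a criterion rather than omitting one, attaches it to the ICER alone, and does not say that net monetary benefit prevails if the two conflict.

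Three stronger readings are tempting and are not supported.

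- A reader might infer that, with one 20-minute appointment and short follow-up, the sign of the QALY difference is a coin toss. That needs a true effect of about zero, and the document gives no figure for it.
- A reader might simulate the two rules, for instance with true values of +£50 and 0 QALY and standard errors of £150 and 0.004, and find that the stated rule passes while the sample's net benefit is negative in about 38% of draws. That is discordance between two rules, not an error rate against the truth: true net benefit in that scenario is -£50, so every positive verdict is false under either rule. About 32 of the 38 points are the dominated quadrant, which the net benefit reported alongside would expose. The inputs are invented, and cost and effect are drawn independently, although the plan intends to allow for their correlation.
- A reader might infer that national rollout hangs on the ICER sentence. Only the Abstract makes the implementation strategy conditional on cost-effectiveness. Box 1 and the Process evaluation section speak of effectiveness, and the Interviews and focus groups and Dissemination sections of positive results.

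**Conclusion.** The point holds as a defect of wording in a stated decision rule. The reversal for negative QALY differences is exact and rests on no assumption. How likely it is to matter does rest on assumptions: utility SD 0.15–0.30, 432 analysed per arm, design effect 1–1.91 (the upper value borrows the primary outcome's ICC and an assumed CV) and a constant utility difference. Within that range it is a real possibility for nil or small effects and unlikely at a utility difference of about 0.05. The document does not show that the trial would end in a wrong conclusion, because the quantity that gives the right answer is already to be reported. What is missing is the statement that this quantity decides. Severity is minor, and the sample size, power and significance level are unaffected.

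**What to change.** Keep the £20 000 threshold and replace the clause on ICERs with a rule such as: *NAT-C is judged cost-effective if expected incremental net monetary benefit at £20 000 per QALY is above zero; the ICER is reported with its quadrant and any dominance, and the below-threshold reading applies only when incremental QALYs are positive.* The cost is one sentence in the protocol or the health economic analysis plan, best settled before outcome data are analysed. It needs no new data and no additional analysis, since expected net monetary benefit is already planned.

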## Process evaluation

A mixed-methods substudy will use normalisation process theory (NPT) to structure data collection and analysis of: (1) implementation of the NAT-C in trial general practices and (2) clinicians’ and staff perspectives on the usefulness and effectiveness of the NAT-C, how this relates to usual care and how, if effective, the NAT-C could be implemented nationwide.

NPT is a well-established framework for understanding the dynamics involved in implementing, embedding and integrating a new intervention. We will draw on quantitative and qualitative elements to identify issues related to implementation in terms of (1) a quantitative NPT survey to elicit the views of clinicians who have undergone NAT-C training and (2) qualitative interviews/focus groups with general practice staff, clinicians and external stakeholders with key roles in health policy and commissioning, relevant to cancer care in primary care.

### Normalisation MeAsure Development Questionnaire survey

The NPT survey (NoMAD instrument) is a 23-item instrument for measuring implementation processes from the perspective of professionals directly involved in the work of implementing complex interventions. During feasibility testing, we adapted the NoMAD instrument in to a 17-point checklist to specifically address the NAT-C. Clinicians will be invited to complete the NoMAD survey either on paper or online following completion of NAT-C training (survey 1). Using results from survey 1, emerging qualitative findings and experiences, the NoMAD will be adapted to include questions regarding emerging issues and concerns. At the end of a practices’ involvement with the study, clinicians who have used the NAT-C will be asked to complete the adapted NoMAD survey (survey 2).

Clinicians will be asked questions on a Likert scale in relation to issues such as: attitudes to the NAT-C, NAT-C training and implementation concerns. Completion of the survey will imply informed consent. Data collection and management for surveys 1 and 2 will be delivered by the University of Hull (UoH). All survey data will be anonymised.

### Interviews and focus groups

Opinion regarding NAT-C training, the role and place of the NAT-C within routine practice will be sought from clinicians who received NAT-C training and experts from a range of stakeholder groups (eg, local commissioning groups, general practice federations, the National Cancer Research Institute’s primary care group, Royal College of GPs, and Macmillan). Semistructured interviews and focus groups using a priori topic guides (either phone/video conferencing or face to face, as appropriate) will be conducted at various time points post-NAT-C use and up to the end of study. Interviews/focus groups with clinicians and key stakeholders will focus on structural and policy issues relevant to potential implementation of the NAT-C in general practices nationwide, should trial results be positive.

Maximum variation purposive sampling will be used to optimise exploration of a range of clinicians, practice staff and key stakeholder perspectives. An initial purposive sampling grid for clinicians (profession, years of clinical practice, randomisation strata) will be expanded with further criteria identified from implementation study survey responses.

A sample of 15–20 clinicians and general practice staff and 10–15 experts from a range of stakeholders will be sought through interviews or focus group.

Potential interviewees will be provided with a study invitation, a study information sheet and asked to provide informed written consent prior to study procedures. All interviews and focus group discussions will be audiorecorded.

### NoMAD survey analysis

Free-text responses in survey 1 will be monitored by the implementation study researcher to enable rapid feedback to inform subsequent training at other sites.^29^

Once all surveys 1 and 2 are completed, free-text responses will be subject to thematic analysis and descriptive statistics will be used to analyse Likert scale responses including: (1) the extent to which the intervention fits with current practice in relation to the components of NPT; (2) the potential relevance of the NAT-C to individuals’ roles; (3) adequacy of NAT-C training and (4) clinician attitudes to the NAT-C at baseline and at the end of the trial from survey 1 and 2.

### Interview/focus group analysis

Qualitative data will be analysed using thematic analysis,^29^ informed by NPT, relating to: how clinicians understand the intervention (coherence); how they engage with it (cognitive participation); enact it (collective action) and appraise its effects (reflexive monitoring).^30^ The end of trial analysis will develop themes in relation to how the NAT-C could be implemented in primary care nationally, should trial be results be positive. Transcripts will be coded line by line.

### Synthesis with intervention uptake data

We will synthesise key aspects of process evaluation data, with effectiveness of the NAT-C within clusters according to randomisation strata, to improve understanding using NPT about how and if the NAT-C should be implemented into clinical practice using critical interpretative synthesis.^31^

Kirkpatrick’s model for training evaluation will be used to evaluate NAT-C training in terms of: reaction to the training, learning and skills improvement, behavioural change and results.^32^ Reaction will be assessed by responses to NoMAD surveys and interview. Learning and behavioural change will be evaluated through qualitative data.

### Trial organisation and governance

CANAssess is sponsored by the UoH coordinated by Leeds CTRU and UoH. The sponsor had no direct input in to the design or conduct of the study. The Trial Management Group consists (TMG) of coapplicants, trial coordinators, four GP-hub leads and a public–patient representative. The TMG is responsible for clinical setup, ongoing management, promotion of the trial, and for the interpretation and publishing of the results. A TSC will meet annually and on request to provide independent oversight of the trial and reports to the Sponsor.

A Data Monitoring and Ethics Committee is not needed due to the nature of the study. The TSC will adopt a safety monitoring role, with the constitution of a subcommittee to review safety issues where necessary.

### Patient and public involvement

An experienced lay representative was part of our funding application. She also reviewed and edited public-facing study documentation, and sits on our TMG, with public–patient involvement as a standing item. A further lay representative forms part of our TSC.

## Ethics and dissemination

### Dissemination

If trial results are positive, the NAT-C has the potential to become the gold standard cancer care delivery in primary care as the only valid tool subjected to formal effectiveness testing.

Findings will be presented and discussed at a final dissemination meeting, to which a wide range of stakeholders will be invited, including trial clinicians, participants and those involved in the stakeholder engagement.

Results of the study will be published in peer-review publications and will be presented at national and international conferences. A lay summary of our findings will be published on study and organisational websites, sent to participating general practices and will be accessible to participants.

### Ethical considerations

The trial received ethical approval from the London-Surrey REC (20/LO/0312). Any future amendments to the trial will be submitted to the REC and participants will be informed of any changes which may affect them.

### Impact of COVID-19

The COVID-19 outbreak in England occurred just as ethical approval for the study had been obtained and the process of site identification had begun. We halted site identification and adapted the trial processes to allow remote intervention delivery as per practice procedure for remote consultations, telephone consent and data collection, and online patient study responses and online completion of follow-up questionnaires. Amidst concerns that patient recruitment may be affected by social distancing measures, the Leeds CTRU also highlighted how their secure online computer systems would allow online informed consent provision and data collection. We; therefore, submitted an amendment to allow all study activity to be completed remotely through phone or videoconference.

### Trial status

Following COVID-19-related delays, the trial team is in place, incorporating employed trial-specific research nurses and Clinical Research Network support. Recruitment of GP practices and participants is underway. Our first study site was opened for recruitment on 21 October 2020 and we now have seven general practices recruiting participants. The first participant was recruited on 1 December 2020. As of 25 January 2022, we have 27 general practices open to recruitment and have recruited 333 patient participants and 102 carer participants. This manuscript has been prepared in accordance with study protocol V.3, 24 June 2020. A copy of the full protocol is available on request from JC.
